### Aims

Using the VISA-A questionnaire as the primary outcome measure, the aim of this study is to compare the effectiveness of Silbernagel’s daily exercise program with progression guided by pain symptoms, against SSC6’s exercise program carried out 3 times per week with specific load targets. We will assess plantar flexor strength using isokinetic dynamometry, reactive strength based on a drop jump, and lower limb biomechanics during a novel single leg horizontal rebound test and running, and investigate whether changes in these variables over the course of the 12-week rehabilitation program are associated with improved pain and function outcomes using the VISA-A questionnaire when comparing the two rehabilitation programs. We will assess participant satisfaction with their prescribed program, adherence and fidelity using a training diary and perform follow-up interviews at 6, 12 and 24 months to analyse participation in their sport and any potential re-injury rates.

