### Primary outcome measure

#### VISA-A questionnaire

The VISA-A questionnaire has been shown to be a valid, reliable and easy-to-use outcome measure tool for intervention studies on AT [46]. It consists of eight questions regarding pain and function during both daily living and sporting activities. The overall score is between 0 and 100 where higher scores represent reduced pain and improved function. An improvement of 21 points between 2 and 12 weeks of a rehabilitation program have been typically observed [44]. While the VISA-A score will not determine eligibility for inclusion into the study, it will be used to map progress over the course of the rehabilitation program and in the follow-up period. The difference in VISA-A score between both training protocols from baseline testing to the outcome testing at 6 weeks, 12 weeks, 3, 6 and 12 months; will formulate the primary outcome measure for this study.

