### Statistical analysis and power calculation

This study is powered to detect a change of 15 points on the VISA-A questionnaire, similar to previous studies investigating clinical changes after a rehabilitation program [61, 62]. The average reported change in a VISA-A questionnaire after a 12-week intervention is 21 points with a standard deviation 6.6 points [44]. Assuming a power of 80% and a two-sided 5% significance level, a total of 25 participants in each group would be required. Allowing for a conservative drop-out rate of 15%, the proposed total sample size is 60, with 30 in each group. This number is similar to those used in other high quality injury rehabilitation RCT studies [40, 45].

Statistical analysis will be performed using R (R Studio version 1.2.5). Descriptive statistics will be used for all continuous variables, and means and standard deviations will be reported. Comparisons between both groups at different timepoints will be assessed using Student’s independent samples two-tailed t-tests. An intention to treat analysis will be used to test a within-group and between-group change in VISA-A questionnaire score at testing and follow-up timepoints, using a repeated measures Analysis of Covariance (ANCOVA). The primary outcome measure - changes to the VISA-A questionnaire, will the dependent variable, group will the between participants factor and time will be the covariate. Non-parametric equivalents (Matt-Whitney U-Test and Friedman Test respectively) will be used if a Shapiro-Wilk test indicates that the assumption of normality has not been met. A multiple regression analysis will be used to investigate the total variance and the relative weight of each independent variable with changes in VISA-A score as the dependent variable. The independent variables will be changes in plantar flexor strength, reactive strength and lower limb biomechanical variables, as well as exercise adherence and fidelity. Effect sizes will be reported using partial eta squared threshold values of > 0.2 (small), > 0.5 (moderate), and > 0.8 (large). Statistical significance will be accepted at α = 0.05.

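### If normality is rejected, the repeated measures ANCOVA of VISA-A is replaced by a Friedman test, which has no group term and cannot test the between-group change

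*Protocol article*

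**What the plan says.** All of the analysis text is in the protocol article, under Statistical analysis and power calculation. Two parametric methods are named in order.

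1. The first is a group comparison per visit: "Comparisons between both groups at different timepoints will be assessed using Student’s independent samples two-tailed t-tests".
2. The second concerns VISA-A: "An intention to treat analysis will be used to test a within-group and between-group change in VISA-A questionnaire score at testing and follow-up timepoints", by repeated measures ANCOVA. Change in VISA-A is the dependent variable, and "group will the between participants factor and time will be the covariate".

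The fallback follows: "Non-parametric equivalents (Matt-Whitney U-Test and Friedman Test respectively) will be used if a Shapiro-Wilk test indicates that the assumption of normality" is not met. The word *respectively* pairs the t-test with Mann-Whitney and the repeated measures ANCOVA with Friedman.

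The question is comparative. Under Aims, "the aim of this study is to compare the effectiveness of Silbernagel’s daily exercise program with progression guided by pain symptoms, against SSC6’s exercise program". Under VISA-A questionnaire, the primary outcome is "The difference in VISA-A score between both training protocols from baseline testing to the outcome testing at 6 weeks, 12 weeks, 3, 6 and 12" (the last three figures being months). The same section describes the scale: "The overall score is between 0 and 100 where higher scores represent reduced pain and improved function".

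**The concern.** The Friedman test is offered as the equivalent of a model whose purpose includes a comparison of two groups, but it compares repeated measurements within one set of participants. If the switch is made, the one longitudinal test of group on the primary outcome disappears. What takes its place is a test that should be significant whenever participants improve over 12 weeks, which the protocol expects under exercise therapy. Such a result says nothing about which program is better.

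The standard Friedman test also uses only participants with every visit recorded. That sits badly with the intention-to-treat statement, the 15% drop-out allowance, and the Discussion's own warning about drop-outs and unreturned follow-up questionnaires.

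Finally, the switch is decided by a test on the trial data, and the protocol does not say which values are tested (raw scores, changes or residuals), at which visits, in which arm, or how many rejections are enough.

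**Working it through.** There is no figure in the plan to reproduce for this point, and the point does not depend on the sample size.

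**Step 1. What the Friedman statistic contains.** For N participants and k visits, with R_j the sum over participants of the within-participant rank at visit j:

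Q = 12 / [N k (k + 1)] × Σ R_j² − 3 N (k + 1)

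No term refers to group. As a check, 50 simulated participants at 3 visits were shuffled, so that any split into two arms changed. The statistic was 1.96 before and 1.96 after.

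**Step 2. How it behaves against the trial's question.** Inputs from the protocol: 25 per group, a difference of 15 points, a mean change of 21 points with SD 6.6, two-sided 5%. Assumptions: visits at baseline, week 6 and week 12; normal data; between-visit correlation 0.5; change linear over visits; 3,000 runs. A second SD of change, 18.75, is assumed because it gives a standardised difference of 15 / 18.75 = 0.8, at which 25 per group has about 80% power: 2 × (1.960 + 0.842)² / 0.8² = 24.5.

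Each cell gives the rejection rate for SD 6.6, then for SD 18.75. Mann-Whitney is applied to change from baseline to week 12.

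| Scenario (change by week 12) | Friedman, all participants | Mann-Whitney |
|---|---|---|
| Both arms +21, no group difference | 100%, 100% | 4.4%, 4.4% |
| Arms −7.5 and +7.5 (15 apart, average flat) | 1.4%, 5.0% | 100%, 75.9% |
| Arms +21 and +36 (15 apart) | 100%, 100% | 100%, 75.3% |

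Friedman gives the same answer in the first and third rows, where the group difference is 0 and 15. In the second row it misses a 15-point difference. It responds to the average time course only.

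**Step 3. Complete rows.** Table 3 collects VISA-A at six points: baseline, weeks 6 and 12, and 6, 12 and 24 months. With 15% drop-out, at most 60 × 0.85 = 51 participants have all six. Each further missed questionnaire removes a participant from a six-visit Friedman test.

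**Step 4. What remains between groups.** Mann-Whitney at each timepoint. Table 3 gives five post-baseline points, and no adjustment is stated. If the five tests were independent, the chance of at least one false positive would be 1 − 0.95⁵ = 22.6%. They are correlated, so this is illustrative. The same holds for the planned t-tests, so the switch does not create it, but the switch leaves nothing else.

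**Step 5. How often the switch would happen.** Assumptions: SD 18.5 at each visit, correlation 0.6, baseline mean 50, 25 per arm, scores capped at 0 and 100, Shapiro-Wilk at 5% at week 12 only, and a rejection in either arm triggers.

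- Exactly normal data: 1 − 0.95² = 9.75%.
- Change scores: about 10%, for a week-12 mean of 71 (50 plus the protocol's 21 points) or 80.
- Raw scores: about 14% for a mean of 71; 58% to 61% across runs for a mean of 80.

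If instead any one of ten tests triggers (2 arms × 5 follow-ups), exactly normal data give 1 − 0.95¹⁰ = 40%. With capping and a mean rising from 50 to 80, simulation gave 39% for change scores and 84% for raw scores.

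**The case against.** The strongest reply is that the same sentence keeps a between-group test. The t-tests fall back to Mann-Whitney, which held its 5% level and detected 15 points in 75% to 100% of runs. A reader might infer that the trial's question would go unanswered after the switch. The document does not support that: an answer between groups remains, as separate tests per timepoint. This part of the reply stands.

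A reader might also infer that the switch is likely because VISA-A is capped at 100. On change scores, which the protocol names as the dependent variable, capping adds essentially nothing (about 10% with or without it at week 12). The high rates need raw scores and an assumed week-12 mean of 80, or an any-of-ten rule that the protocol does not state.

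Nor has inflation of the error rate been shown. When the two-stage rule for the between-group comparison (Shapiro-Wilk, then t-test or Mann-Whitney) was simulated with no group difference, it rejected in 4.6% of normal trials and in 5.1% to 5.5% of capped ones. The 100% for Friedman is not a false-positive rate for its own hypothesis either, since participants did change over time.

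Two smaller points are fair. The ANCOVA is also meant to test within-group change, and Friedman can address that part. And a classical repeated measures analysis may need complete rows too, so the missing-visit point is secondary to the missing group term.

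None of this makes Friedman an equivalent of a model with a group factor. Running it in each arm and comparing the two p-values is not a between-group test.

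**Conclusion.** The fallback is wrong as written. The Friedman test cannot test the between-group change that the repeated measures ANCOVA is meant to test, and this follows from its formula without any simulation. If the switch is made, the longitudinal group comparison on the primary outcome is lost, participants with a missed visit are dropped, and the between-group question rests on per-timepoint Mann-Whitney tests with no baseline adjustment and no stated multiplicity adjustment. A significant Friedman result would show only that participants changed over time.

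The chance of the switch is uncertain. With the week-12 either-arm rule it is about 10% for change scores and about 14% to 60% for capped raw scores, under the assumed SD, correlation and means. It would be higher under an any-of-ten rule. The protocol does not fix the choices that decide this.

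**What to change.** - Delete the Shapiro-Wilk switch to Friedman for VISA-A.
- Keep the planned longitudinal analysis whatever a normality test shows, and state that it contains group and group-by-time terms. The protocol currently names group and time only.
- Check model residuals by plot.
- Pre-specify one between-group sensitivity analysis of the VISA-A change: permutation, bootstrap or a rank-based method that carries a group factor.
- If Friedman is kept, confine it to a descriptive within-group result and say that it is not evidence for either program.

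The cost is a few sentences of analysis text and one extra sensitivity run. Design, visits and sample size are untouched. Under Trial status, 18 participants had been included by November 2020 and data collection was expected to run to April 2023, so the change could be made before the analysis.

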#### Training diary

In order to determine adherence and fidelity with the rehabilitation program and pain response to exercise, each patient will be required to complete a training diary logging their completed running and rehabilitation sessions as well as reporting any pain symptoms using a numerical pain rating scale (NPRS), that will be reviewed at week 6 and returned at week 12. Adherence is defined as the proportion of prescribed exercises completed while fidelity refers to whether the participant completed the prescribed exercises, sets, repetitions and target loads. Participants will be advised to take an extra recovery day between exercise sessions if pain was above 5/10 on the day after a session and to adjust their loads for the subsequent session.

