### Interventions

Each participant will be prescribed a graded rehabilitation exercise training program which they will perform at home or in a local gym. However, they will present themselves for one supervised session every 2–3 weeks by their respective group investigators to ensure compliance and appropriate progression. The patients following Silbernagel’s training program [see Table 1] will perform solely calf strength exercises with self-prescribed additional resistance and will progress their exercises based on a NPRS, where there is no greater than a 4/10 pain response during and in the 24 h following a training session. They will then progress to plyometric exercises as tolerated. The SSC6 group [see Table 2] will follow a multifactorial exercise program comprising of bilateral and unilateral kinetic chain strength, calf strength and plyometric training as well as running drills as early as they can tolerate them. The participants will enter at the highest level where they meet the minimum criteria. For the calf exercises, they will be encouraged to lift a certain percentage of bodyweight in additional resistance and increase weekly. A certain level of pain within tolerable limits will be accepted and participants will be encouraged to increase their resistance loading weekly so long as that pain doesn’t increase. Progression to Level 4 of the program will be based on achieving their prescribed exercise load targets and achieving a deficit of less than 10% between injured and uninjured limbs on the isokinetic strength tests. The reactive strength exercises will be performed at near maximal intensity for a set number of repetitions with good competency and within tolerable pain limits. The participants will progress to Level 5 when they can perform 10 single leg hops with a score of < 4/10 on the NPRS and progress from Level 5 when single leg RSI deficits are < 10%. Outcome measures will be monitored at the various timepoints and will be tracked according to reported NPRS ratings. In both groups, participants will be permitted to begin running in phase 2 when pain during daily activity is < 2/10 but will be advised on periodising their running and rehabilitation exercises throughout the week. Each participant will be provided with a training log in order to monitor training loads. Should an adverse event occur which results in re-injury or a new injury, the participant will be instructed to contact their respective investigator immediately so that they can be examined and their treatment will be adjusted, postponed or discontinued where appropriate. Upon completion of the training intervention, participants in both groups will be given a maintenance training program for 6 months. The design, prescription and reporting of the training intervention meets all of the 16-item checklist requirements in the Consensus on Exercise Reporting Template (CERT) [60] [Available in supplementary files].

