Our study will include a sample of participants who practise running-based sports and are of a particular age profile (age 18–45), have had no injection therapies in the previous 6 months and no co-existing lower limb injuries. Like most studies of similar design, there is a high risk of drop-outs, poor compliance with the respective programs and failure to respond to the follow-up questionnaires. This will be managed by aiming for a higher number of participants than the study is powered for and maintaining regular communication with the participants.

In summary, this two-arm RCT will compare the effectiveness of a criteria-based rehabilitation program with progression guided by achieving functional outcome measures with an evidenced-based program where progression is guided solely by pain symptoms. The results of this study will provide insights as to whether improved strength, reactive strength and lower limb biomechanics are associated with reduced pain in patients with chronic mid-portion AT and assist clinicians treating this injury to set objective criteria to progress rehabilitation and return to sport.

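### The VISA-A regression omits group and baseline VISA-A, could take in up to about 35 candidates for about 50 completers, and relies on fidelity and hop-test changes that do not fit it

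*Protocol article*

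**What the plan says.** Under Statistical analysis and power calculation, the article states: "A multiple regression analysis will be used to investigate the total variance and the relative weight of each independent variable". The outcome is change in VISA-A; the sentence gives no time window. The next sentence lists the independent variables: change scores for calf strength, for reactive strength and for lower-limb biomechanics, together with adherence and fidelity. Group and baseline VISA-A are not listed. In the same section, the repeated measures ANCOVA does name group as a factor.

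The Aims say that these associations will be examined in the context of comparing the two programs. The Discussion adds: "The results of this study will provide insights as to whether improved strength, reactive strength and lower limb biomechanics are associated with reduced pain".

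Under Training diary, "fidelity refers to whether the participant completed the prescribed exercises, sets, repetitions and target loads". Under Interventions, control participants "will perform solely calf strength exercises with self-prescribed additional resistance". Table 1 nevertheless gives the control arm named exercises with sets and repetitions. Table 3 and the Investigations paragraph place the drop jumps and the single-leg hop test at weeks 6 and 12 only.

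**The concern.** The two programs are built to differ in what the predictors measure. SSC6 has load targets tied to bodyweight, kinetic-chain work and criteria-based reactive strength training; the control program is calf work with resistance chosen by the participant. Program can therefore move both the predictors and VISA-A. In a pooled model without group, a difference between programs can appear as the effect of strength or reactive strength. Omitting baseline VISA-A leaves starting severity free to do the same.

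The stated outputs are the variance explained and the weight of each variable. Both are sensitive to the number of predictors relative to participants. A reader could take a high R-squared as evidence that these qualities account for recovery, and the Discussion hopes to help clinicians set objective criteria on this basis.

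**Working it through.** **1. Completers.** The plan gives "This study is powered to detect a change of 15 points on the VISA-A questionnaire", "21 points with a standard deviation 6.6 points", "Assuming a power of 80% and a two-sided 5% significance level" and "a total of 25 participants in each group would be required". The usual two-mean formula gives n = 2(1.96 + 0.84)² × 6.6² / 15² = 3.04, so 4 per group (5 with the t distribution). The stated 25 is not reproduced. That is a separate matter; only the number of completers is needed here. The dropout step does reproduce: 25/0.85 = 29.4, so 30 per group and 60 in total. Completers are 2 × 25 = 50, or 60 × 0.85 = 51.

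**2. Candidate predictors.** The article names families, so this count is a reconstruction. It assumes one value per measure, one limb and three joints.

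| Family | Measures | Count |
|---|---|---|
| Isokinetic strength | two knee positions | 2 |
| Drop-jump RSI | double and single leg | 2 |
| Running | four spatiotemporal, leg stiffness, three joint angles | 8 |
| Hurdle hop | two distances and contact time (3), ground reaction forces (3), vertical and leg stiffness (2), joint stiffness (3), powers (3), moments (3), angles (3) | 20 |
| Diary | adherence, fidelity | 2 |
| Total | | 34 |

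Taking one variation at a time, the total is 33 without hip stiffness, 35 with a hurdle-hop RSI, and 36 with the two strength asymmetries. Entering both limbs would add more.

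**3. R-squared by chance.** With p predictors and no true association, the expected R-squared is p/(n − 1), and its distribution is Beta(p/2, (n − p − 1)/2). At n = 51:

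| p | Residual df | Expected R-squared | 95th percentile |
|---|---|---|---|
| 5 | 45 | 5/50 = 0.10 | 0.21 |
| 12 | 38 | 12/50 = 0.24 | 0.39 |
| 20 | 30 | 20/50 = 0.40 | 0.56 |
| 26 | 24 | 26/50 = 0.52 | 0.68 |
| 35 | 15 | 35/50 = 0.70 | 0.84 |

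At n = 50 and p = 35 it is 35/49 = 0.71, with 14 residual df.

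Suppose instead that the true R-squared is 0.30 (an assumption, with independent normal predictors). The simulated mean observed R-squared is 0.36 with 5 predictors and 0.79 with 35. Power of the overall F test is about 0.94 and 0.26. Under independent predictors and equal residual variance, a coefficient's standard error is larger with 35 predictors than with 5 by √((51 − 7)/(51 − 37)) = √(44/14) = 1.77.

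**4. Baseline VISA-A.** With equal SDs and a baseline-to-follow-up correlation ρ, the correlation of change with baseline is −√((1 − ρ)/2). The documents give no ρ. Over an assumed range of 0.3, 0.5 and 0.7 it is −0.59, −0.50 and −0.39. A strong predictor of the outcome is therefore left out; it biases a given weight to the extent that the weight's variable is also related to baseline severity.

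**5. Fidelity.** The definition has four parts: exercises, sets, repetitions and target loads. SSC6 prescribes all four. The control arm prescribes the first three, and its resistance is self-chosen. The same score therefore rests on different content in each arm.

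**6. Timing.** The two RSI and 20 hurdle-hop measures, 22 of the 34, have no baseline. Their change can run only from week 6 to week 12, while strength, running and VISA-A changes can run from baseline. If VISA-A change is taken from baseline, the windows do not match.

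**The case against.** The strongest reply is that the article fixes no list. It names families, it introduces the hop biomechanics as examples, and the choice of predictors is commonly left to a fuller document that is not shown. This stands. A reader might infer that the regression will enter about 35 variables and that its results will be largely noise. The documents do not say so: 35 is an upper reconstruction, and chance R-squared passes one half only at about 26 predictors. The article also does not say whether R-squared will be unadjusted.

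A reader might also infer that the control arm cannot have a fidelity score. That is wrong, because Table 1 prescribes its exercises, sets and repetitions; only the load part is undefined. Nor is adherence shown to be a stand-in for arm because one program is daily and the other mostly three times a week. It is defined as the share of each participant's own prescription that was done, so it is already scaled.

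Finally, this is a secondary association analysis, and the Discussion promises insight, not proof. That limits the consequence. It does not answer the omission of group and baseline VISA-A, because the article states what the independent variables will be and neither is among them.

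**Conclusion.** The point holds in a limited form and is worth correcting before analysis. Three parts do not depend on how many predictors are entered: group and baseline VISA-A are absent from a stated list; the load part of fidelity is not comparable between arms; and hop-test changes can cover only weeks 6 to 12.

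The size of the overfitting does depend on the number. Chance R-squared is about 0.70 if all named measures enter, 0.40 at 20 and 0.10 at 5, with 50 to 51 completers. The upper figure rests on one limb, three joints and every named measure being used. The distortion from omitting group or baseline cannot be sized from the documents; the range of −0.59 to −0.39 rests on assumed correlations and equal SDs.

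**What to change.** - Always include group and baseline VISA-A in the model.
- Pre-specify a short set drawn from each named family, including running and hop biomechanics, since the Aims and Discussion make these part of the question. As an illustration and not a cap, one measure from each of strength, reactive strength, running and hop, plus adherence, group and baseline VISA-A, makes 7 terms: chance R-squared 7/50 = 0.14, with 43 residual df. If the full list is kept, use penalised regression.
- Report adjusted or cross-validated R-squared, and label the analysis exploratory.
- In the pooled model, score fidelity on exercises, sets and repetitions only, or report it by arm.
- For drop-jump and hop measures, use the week-12 value or the week 6 to 12 change, and state a matching VISA-A window.

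The cost is analysis wording; group and baseline VISA-A are already recorded. The downside is that fewer variables are tested in one model and the explained variance will look lower.

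### Cut-offs of 0.2, 0.5 and 0.8, which belong to Cohen's d, are attached to partial eta squared, so most non-trivial effects would be labelled one or more grades too low

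*Protocol article*

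**What the plan says.** The section Statistical analysis and power calculation of the protocol article fixes both the effect-size measure and its verbal grades: "Effect sizes will be reported using partial eta squared threshold values of > 0.2 (small), > 0.5 (moderate), and > 0.8 (large". The rule is not limited to any outcome, so it covers the primary VISA-A comparison as well as the secondary measures. VISA-A is to be analysed "using a repeated measures Analysis of Covariance (ANCOVA"), with group as the between-participants factor and time named as the covariate. Adjustment for the baseline score is not mentioned.

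The same section gives the planning figures that can be used to judge the grades: "This study is powered to detect a change of 15 points on the VISA-A questionnaire"; "The average reported change in a VISA-A questionnaire after a 12-week intervention is 21 points with a standard deviation 6.6 points"; "Assuming a power of 80% and a two-sided 5% significance level"; "a total of 25 participants in each group would be required".

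**The concern.** The values 0.2, 0.5 and 0.8 are the familiar benchmarks for a difference in means divided by a standard deviation. That quantity has no upper bound. Partial eta squared is a proportion of variance and cannot exceed 1. On that scale, a limit of 0.8 requires group membership to explain 80% of the relevant variance. The article states the measure and the limits together, and they do not belong together. Nothing elsewhere in the article corrects this.

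What is at stake is how the results are read. The Discussion leaves open whether the target-driven programme gives comparable outcomes sooner. A real between-group difference described as less than small could be misread as evidence that the programmes are alike. The summary also says the findings are meant to help clinicians set progression criteria, and such readers may rely on the labels.

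**Working it through.** **Inputs.** All but the last come from Statistical analysis and power calculation: the grades >0.2, >0.5 and >0.8 on partial eta squared; a target of 15 VISA-A points; SD 6.6; 80% power; two-sided 5%; 25 per group before drop-out; 15% drop-out. The 0–100 range of VISA-A is in the section on the primary outcome measure.

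**1. The plan's own figure.** The normal approximation is n per group = 2 × (1.960 + 0.842)² / d² = 2 × 7.85 / d².
- Printed inputs: d = 15/6.6 = 2.27, so n = 15.7/5.17 = 3.04, that is 4 per group (5 by the t-test). The stated 25 is not reproduced.
- Trying d = 0.8: n = 15.7/0.64 = 24.5, that is 25 per group (26 by the t-test). This matches.
- Solving back from n = 25 gives d = 0.79 (normal) to 0.81 (t-test). For 15 points, that implies an SD of 15/0.79 = about 18.9 to 15/0.81 = about 18.5.
- The drop-out step does reproduce: 25/0.85 = 29.4, so 30 per group and 60 in total.

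So two different standardised effects can be read from the section: 2.27 from the printed SD and about 0.8 from the stated sample size. Both are carried forward.

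**2. Conversion.** For two equal groups with no other terms, the between-group variance is d²/4 in units of the within-group variance. Hence eta² = d²/(d² + 4) and d = 2√(eta²/(1 − eta²)).

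| d | eta² |
|---|---|
| 0.2 | 0.04/4.04 = 0.0099 |
| 0.5 | 0.25/4.25 = 0.059 |
| 0.8 | 0.64/4.64 = 0.138 |
| 2.27 | 5.17/9.17 = 0.56 |

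| Plan's limit (eta²) | Equivalent d | Points at SD 6.6 | Points at assumed SD 18.5 |
|---|---|---|---|
| 0.2 'small' | 2√(0.2/0.8) = 1.0 | 6.6 | 18.5 |
| 0.5 'moderate' | 2√(0.5/0.5) = 2.0 | 13.2 | 37 |
| 0.8 'large' | 2√(0.8/0.2) = 4.0 | 26.4 | 74 |

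The SD of 18.5 is not in the document. It is the value implied by 25 per group and is shown only to give a range.

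**3. Which labels change.**

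| eta² | Label on the converted d scale | Label under the plan |
|---|---|---|
| below about 0.01 | below small | below small |
| 0.01 to 0.06 | small | below small |
| 0.06 to 0.14 | moderate | below small |
| 0.14 to 0.2 | large | below small |
| 0.2 to 0.5 | large | small |
| 0.5 to 0.8 | large | moderate |
| above 0.8 | large | large |

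An effect of d = 0.8 (eta² 0.138, or about 0.143 as the sample value at 25 per group) is at the border of 'large' by convention and below 'small' under the plan. The 15-point target at SD 6.6 (eta² 0.56) is well inside 'large' by convention and 'moderate' under the plan.

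**4. Sensitivity to covariate adjustment.** If baseline adjustment is assumed, with correlation ρ between baseline and outcome, d is replaced by d/√(1 − ρ²). For d = 0.8, partial eta squared is 0.15 at ρ = 0.3, 0.18 at 0.5, 0.20 at 0.6 and 0.24 at 0.7. It therefore stays at or below the plan's 'small' limit up to ρ of about 0.6.

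**The case against.** The strongest reply has three parts.

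First, a reader might infer that the effect the trial is sized for would be reported as less than small. The printed figures do not support that. With 15 points and SD 6.6, eta squared is 0.56 and the label is 'moderate'. The result below 'small' follows only from the effect of about 0.8 implied by 25 per group. The gap between the two arises because the sample size does not follow from its printed inputs, which is a separate matter. Likewise, the limits of 18.5, 37 and 74 points rest on a back-calculated SD. This part stands, so both readings are given above.

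Second, a reader might infer that every effect label would be wrong. That is not so. Trivial effects are rightly left ungraded, and very large ones keep their grade. For example, the plan also tests within-group change. Reading 6.6 as the SD of change, 21/6.6 = 3.18, and with 25 participants partial eta squared is 25 × 3.18²/(25 × 3.18² + 24) = about 0.91, correctly called 'large'. This part also stands.

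Third, the simple conversion ignores the planned repeated measures model. That is fair: the exact equivalents depend on the model terms, and with a baseline correlation of 0.7 an effect of d = 0.8 would just pass the 'small' limit. But it would then be called 'small' rather than 'large', so the mismatch shrinks without going away.

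It is also true that only adjectives are at issue. Group means and SDs will be reported, and readers can compare a difference with the 15-point yardstick themselves.

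**Conclusion.** The concern holds for the labelling rule. As written, the plan grades partial eta squared with limits that belong to Cohen's d. For a two-group comparison without covariates, those limits amount to d = 1.0, 2.0 and 4.0. An effect of d = 0.8 falls below 'small', and the 15-point target at the printed SD is called only 'moderate'. Every label that changes is too low, and none is too high.

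The conclusion rests on the equal-group conversion without covariates. The baseline-adjusted figures are an assumption, since the protocol states no such adjustment. A reader should not infer that the trial's inference is compromised: the hypothesis tests, p-values and sample size do not use these grades. This should be fixed because it bears on interpretation, but it is not a flaw that invalidates the analysis.

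**What to change.** Replace the sentence with one of two consistent pairings:

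- report Cohen's d (or Hedges' g) with limits of 0.2, 0.5 and 0.8, stating which SD is used to standardise; or
- keep partial eta squared with limits of about 0.01, 0.06 and 0.14.

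The first option is easier to relate to a difference in VISA-A points. The cost is one sentence, with no effect on recruitment, data collection or the tests. The Trial status section reports 18 participants included by 9 November 2020 and data collection expected to run to April 2023. On that timetable the change can be made and dated before analysis, so that it does not look prompted by the results.
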